### Data management

All data will be collected through online surveys and automatically saved by the system, resulting in an electronic dataset generated by online survey platforms. A system-generated respondent ID will be assigned to each response of participants and is to be stored in an accessible, safe, confidential manner (e.g., store the dataset in a file with a password which will only be available for researchers to access). All datasets and backup files will be maintained for 3 years after the study is completed.

### Research ethics and dissemination

The Institutional Review Board of the Hong Kong Polytechnic University (HSEARS20230321008) has approved this study. The intervention protocol was pre-registered in the HKU Clinical Trials Registry (ref: HKUCTR-3012), and strictly followed the CONSORT guidelines [47, 48]. Participants will be asked to read and sign the digital informed consent before participation. The consent will be automatically obtained and saved in the online system, which allows researchers to download and examine. Participants will voluntarily join the study and have the right to drop out at any time without any punishment or need to seek permission. All the responses and personal information are highly confidential, which will be accessed by a password that only researchers know and be destroyed 3 years after the study ends. This study will not cause any harm, and participants are indicated to seek help from school counselors or teachers if having any discomfort. They can also get further support from the additional resources for referral services provided at the end of the survey. We will not report individual data or identifiable information of the participants.

The trial results will be communicated to participants, healthcare professionals, and the public via publication. The full protocol can be accessed through the Open Science Framework (OSF). We will not grant public access to the participant-level dataset due to confidentiality of participants’ personal information, and statistical code can be obtained upon request.

### Protocol amendments

A formal protocol amendment will be required if the modifications to the protocol may significantly affect the conduct of the study and participants’ benefits or rights. Such amendment aspects include changes in study objectives, study design, target population, sample sizes, procedure, and implementation strategies on intervention, etc., which will seek approval from the Institutional Review Board of the Hong Kong Polytechnic University (IRB) before the implementation. Minor modifications that would not affect the conduct of the study, such as corrections or clarifications to the protocol, will also be documented and notified to IRB for further approval. Trail registry will be notified for any protocol amendments as well.

## Results

Recruitment starts in April 2023. We expect to complete data collection before November 2023 and make the results available in 2024. The publications are expected to be available in 2024.

## Discussion

This study is to evaluate a randomized trial of a brief digital growth mindset intervention on enhancing Chinese university students’ help-seeking and sense of control over mental health in the Greater Bay Area. Previous research provided strong empirical evidence about the association between growth mindsets regarding negative emotions and mental health [23–25], yet no intervention study provide supports on its effectiveness on promoting mental health among university students. Besides, the single-session brief digital intervention was demonstrated to be effective, which is comparable to interventions that take several months, and the effects exist even after a 9-month follow-up [28]. Therefore, we anticipate that the brief digital growth mindset intervention, which instills the belief-in-change regarding negative emotions, will significantly enhance participants’ perceived control over anxiety and help-seeking tendency, increase psychological well-being, proactive coping, such as physical activity, and reduce hopelessness, depression, anxiety, and stress symptoms. Moreover, the subgroup analysis will help identify the effectiveness and acceptability in specific groups of participants.

## Significance

Scalable intervention for mental health promotion among university students is in pressing need. Brief digital intervention is a novel and promising initiative to address this need, particularly for university students who have full access to digital devices. This study, examining the effectiveness and acceptability of single-session intervention on growth mindset for university students (U-SIGMA), will serve as a building block for the further development of tailored-made brief cost-efficient intervention for university students, contribute to the theoretical and practical progress of digital psychiatry, and bring benefits to the Hong Kong and mainland Chinese university students and beyond.

## Limitations

There are limitations for further improvements. First, this study targets community samples and includes all participants who pass the attention-checking for data analysis. The efficacy of reducing anxiety and depressive symptoms for intervention may not be significant in participants without anxiety or depressive symptoms or with low levels of anxiety and depression in self-report assessments. Nevertheless, sub-group analyses based on the severity of anxiety and depressive symptoms will be conducted. We can also explore the relationship between motivation of participation and the severity of symptoms in sub-groups. Second, due to the unpredictable number of participants from different universities and different cities, the multi-site comparison may not be feasible due to the uneven number of participations from each site.

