## Methods

### Study design

For this randomized controlled trial study, invitations for participation will be sent to the teachers of six universities in the Greater Bay Area, and then they will be asked to forward the invitation to WhatsApp or WeChat student groups. We also recruit through mass email and promotion posters. Students who click on the research link will be invited to read the research information sheet and sign the consent form, and the survey will immediately end for those students who do not agree to participate in the study without signing the consent. *Qualtrics* in Cantonese and *WenJuanXing* survey tool in Mandarin will be used for Hong Kong students and Mainland students respectively. Participants will be randomized into the intervention group or the waitlist control group by adding a “Randomizer” block into the survey flow of two online survey platforms. The expected allocation ratio and concealment can be ensured since the “Randomizer” block will only appear after the baseline assessments have been completed by the participants and conduct the allocation based on a predetermined ratio. Participants assigned to the intervention group will start the intervention instantly, and those in the control group will receive the intervention link after 8 weeks. Three repeated assessments of the measures will be conducted for two groups simultaneously at (i) baseline, (ii) 2-week post-intervention, and (iii) 8-week post-intervention via survey systems *Qualtrics* (for Hong Kong students) and *WenJuanXing* (for mainland students). The design of 2-week and 8-week post-tests is based on the extant studies on single-session or brief intervention [12, 27]. Invitations for follow-up surveys will be sent to the participants who complete the survey at baseline. Each participant will receive incentives (e-voucher or online red packet) with approximate values of US $5 and US $8 when completing the 2-week and 8-week follow-up questionnaires respectively. Thus, the total compensation for participation is US $13. Incentives will be sent to the participants automatically through the online system excluding invalid responses after the screening. The study flow is seen in Fig. 1.

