### Measurements

Assessments will consist of demographic information and three major parts: (1) fidelity checking measures, including mindsets of negative emotions and intervention feedback, which involves Likert-scale rating of the acceptability of the intervention and open-ended questions for feedback; (2) primary outcome measures, including perceived control over anxiety, attitude toward help-seeking, and hopelessness; (3) secondary outcome measures, including the psychological wellbeing, physical activity, depression, anxiety, and stress symptoms. Two attention-checking items are embedded in all assessment points’ surveys to screen careless responding.

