### Data analyses

An intention-to-treat analysis will be conducted, and multiple imputation will be applied to handle the missing data. Descriptive statistics will be used to demonstrate the socio-demographic and all baseline outcome variables by study arms. Outcome variables will be compared between the arms using *t*-tests, one-way analysis of variance. Generalized estimating equations (GEE) will be used for follow-up data over time. Subgroup analysis will be conducted to test the differences among participants of different gender, motivation, and feedback about the intervention and among participants with different levels of anxiety and depression. Two-level analyses are to be conducted since cluster randomization is used [46]. The group effect, the time effect, and the time-by-group interaction effect on the primary and secondary outcomes will be tested with multilevel regression. A *p*-value of < 0.05 signifies statistical significance, and all statistical analyses will be conducted with SPSS Version 26.

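### Limiting the analysis to participants who pass attention checks, some of them answered after randomization, conflicts with the promised intention-to-treat analysis

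*Protocol article*

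**What the plan says.** Four sections of the protocol article bear on who is analysed.

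- **Data analyses** sets the principle: "An intention-to-treat analysis will be conducted, and multiple imputation will be applied to handle the missing data".
- **Limitations** describes the analysed sample differently: the study "includes all participants who pass the attention-checking for data analysis".
- **Measurements** says when the checks are made: "Two attention-checking items are embedded in all assessment points’ surveys to screen careless responding".
- **Study design** fixes the order of events. The Randomizer block "will only appear after the baseline assessments have been completed by the participants", and there are two later surveys, at 2 and 8 weeks. It also mentions screening once, in connection with payment: "Incentives will be sent to the participants automatically through the online system excluding invalid responses after the screening". The incentives described there are for the 2-week and 8-week questionnaires.

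The article does not say that exclusion is limited to the baseline check. It does not say that a failed follow-up survey is set to missing while the participant stays in the analysis. It does not call the attention-pass group a modified intention-to-treat set or a sensitivity set.

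**The concern.** Intention-to-treat keeps every randomized participant in the arm assigned, whatever happens afterwards. A rule that admits only those who pass checks made partly after allocation selects on post-randomization behaviour, and the arms need not be selected alike.

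They have different experiences before the follow-up checks. By 2 weeks the intervention arm has had a 30-minute digital module, and it is then sent four weekly booster posters. The waitlist arm has had neither. Attentive answering could plausibly depend on that exposure, and on symptoms and motivation, which the Hypotheses section expects to modify the effect. If failures differ between arms and those who fail differ in outcome, the comparison of the remaining participants is no longer protected by randomization.

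The rule may also cost power. The sample size allows for 20% attrition and ends exactly at the required number, so any exclusions beyond that 20% come out of the 200 needed.

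**Working it through.** **1. The statements side by side.** The checks are at baseline, 2 weeks and 8 weeks. Allocation happens once baseline is complete. One check therefore precedes allocation and two follow it. The Limitations sentence is about participants, not single responses, and names no survey. Applied as written, it can remove a randomized participant who fails at 2 or 8 weeks. The Data analyses section would keep that participant. Both cannot describe the same primary analysis.

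**2. The plan's own sample size.** Inputs from the Sample size section: d = 0.40, power 0.80, two-sided alpha 0.05, attrition about 20%.

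- Normal approximation: n per arm = 2 × (1.960 + 0.842)² / 0.40² = 98.1, rounded up to 99 (198 in total).
- Two-sample t-test: 99.08, rounded up to 100 per arm (200 in total), with power 0.804.
- Attrition: 200 / (1 − 0.20) = 250.

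The stated 200 and 250 are both reproduced. Since 250 × 0.80 = 200, nothing is left over for further exclusions.

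**3. Power, illustration only.** Assume that a share *a* of those remaining after 20% attrition is also excluded, equally in both arms. Then n per arm = 125 × 0.80 × (1 − a), and the number to randomize to keep 200 is 200 / [0.80 × (1 − a)].

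| a (assumed) | n per arm | Power at d = 0.40 | Number to randomize for 200 |
|---|---|---|---|
| 0% | 100 | 0.804 | 250 |
| 5% | 95 | 0.783 | 264 |
| 10% | 90 | 0.761 | 278 |
| 15% | 85 | 0.737 | 295 |

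**4. Bias, illustration only.** Suppose that there is no true effect, that shares *f* (intervention) and *g* (control) are excluded, and that excluded participants score D standard deviations worse than those retained in the same arm. The retained mean exceeds the full-arm mean by D × f in one arm and D × g in the other, so the spurious difference is D × (f − g).

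- f = 10%, g = 5%, D = 0.3: 0.3 × 0.05 = 0.015 SD.
- f = 15%, g = 5%, D = 0.5: 0.5 × 0.10 = 0.05 SD, which is 0.05 / 0.40 = 12.5% of the planned effect.

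If f = g, the spurious difference is zero under these assumptions. None of f, g, D or a is in the article.

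**The case against.** The best defence is that no single sentence says that failing any survey removes the participant. Measurements gives the purpose of the checks but no consequence for failing one. The Limitations sentence is mainly about the breadth of a community sample, and the screening sentence in Study design concerns invalid responses and payment. If only the failed survey were voided and then imputed, the plan could be consistent with intention-to-treat. If only the baseline check excluded anyone, exclusion could not depend on the arm. A fuller protocol is said to be available elsewhere, and handling of this kind is often left to it.

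Part of this stands. Exclusion at any survey is an inference from Measurements and Limitations read together, and the baseline check is harmless for the comparison of arms. But the payment sentence indicates that follow-up surveys are screened, and the Limitations wording is about participants. This is a conflict between two current statements, not a detail left out: a fuller document would have to depart from one of them.

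The illustrative figures are also open to challenge. The Sample size section does not define attrition, so unusable responses may already be within the 20%.

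Two stronger readings are tempting and not supported:

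- **Students who abandon the module lose follow-up, in the intervention arm only.** A reader might infer this from "Invitations for follow-up surveys will be sent to the participants who complete the survey at baseline". But the Randomizer appears only once the baseline assessments are done, so everyone randomized has already completed them, and nothing counts the module as part of the baseline survey.
- **The survey flow must be rebuilt so that the check comes before the Randomizer.** Excluding on the baseline check cannot depend on allocation, so validity does not require this. With recruitment planned to finish around August 31, 2023 (Trial status), it is probably too late as well.

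**Conclusion.** The concern holds as a conflict of wording with a real consequence. As written, the analysis set can leave out randomized participants on behaviour measured after allocation, against the stated intention-to-treat analysis. The article allows exclusions that differ by arm; it does not show that they will occur.

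The size is unknown. Under the assumed exclusion rates, power falls from 0.80 to between 0.78 and 0.74, provided that these exclusions come on top of the 20% attrition. Under the assumed arm differences, the bias is about 0.015 to 0.05 SD. The conclusion rests on the text and not on these figures.

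**What to change.** - Define the primary analysis set as all randomized participants, in the arm assigned.
- Set a follow-up survey that fails the attention check to missing for that visit, keep the participant, and handle the gap by the multiple imputation already planned.
- Report attention-check failures by arm and visit.
- Run two sensitivity analyses: one with all responses as recorded, one restricted to participants who pass the checks.
- Reword the Limitations sentence to agree with Data analyses.

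The cost is a little more analysis work and somewhat noisier data, since participants who answered carelessly at some point stay in. Recruitment, sample size and survey flow are unchanged. The change settles who is analysed; it does not fully restore the information lost when a survey is voided, and the imputation still rests on its own missing-data assumption. That is why the as-recorded analysis and the counts by arm should be reported with it.

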## Conclusion

This study presents the protocol of a two-arm waitlist-control randomized controlled trial study for the examination of a digital single-session growth mindset intervention for university students’ mental health. The current study will provide pioneer evidence for the feasibility of implementing tailored, easy-access, scalable, and brief digital interventions among university students in Chinese contexts.

## Trial status

The protocol version is 1.0, and the version date is May 20, 2023. Recruitment started from on April 21, 2023, and the approximate recruitment completed date is August 31, 2023.

## Data Availability

Not applicable.

## Abbreviations

SIGMA: Single-session Intervention on Growth Mindset for adolescents
U-SIGMA: Single-session Intervention on Growth Mindset for university students
MDASS: Mindset of Depression, Anxiety, and Stress Scale
TFA: Theoretical framework of acceptability
ACQ-EC: Emotion Control subscale of Anxiety Control Questionnaire
ATSPPH: Attitude toward Seeking Professional Psychological Help Scale
WEMWBS: Warwick-Edinburgh Mental Well-being Scale
GPAQ: Global Physical Activity Questionnaire
GAD-7: Generalized Anxiety Disorder-7
PHQ-9: Patient Health Questionnaire-9
PPS: Perceived Stress Scale
